## Interventions

3

### Treatment plan

3.1

Participants in the 2 groups will receive the same kind of education about COPD. The contents include smoking cessation, nutrition support, inhalation techniques, coughing techniques, and knowledge of COPD.

The control group will only be treated with standard COPD drugs, while the trial group will perform TNHCG exercises apart from standard drug treatment.

Participants in the trial group will perform TNHCG exercises five times a week, totally 30 minutes per time, for 24 weeks. Before the start of the trial, a designated person (a nurse or rehabilitation physician not involved in conducting this study) will guide the participants on how to perform TNHCG exercises at our hospital. Participants will be required to practice until their movement and breathing are coordinated. If a patient is discharged from the hospital, a designated person will keep in touch with them and continue to guide them through telephone, video, and WeChat every week. The specific exercise content of TNHCG is shown in Figure 3.

**Figure 3 F3:**
[figure not shown]
The content of TNHCG includes Based movement, Warm-up and stretching exercise, Tortoise-shaped exercise, and Acupoint massage.

### Monitoring of exercise intensity

3.2

There are numerous methods to monitor the intensity of exercise, such as the patient's heart rate (HR), subjective symptoms, and maximum oxygen uptake. In clinical practice, we often use the patient's target HR and conscious feelings as monitoring indicators. The patient's HR during exercise should be less than the target HR. The formula to calculate target HR is as follows^[18]^: target HR = [(220 - age) - resting HR] ^∗^ %HRR + resting HR. This method requires professional instructors to determine the patient's resting heart rate before exercise. In our trial protocol, participants’ self-perception is used as the monitoring indicator. During exercise, the target exercise intensity is as follows: the patient does not feel tired and sweats slightly throughout; there are no breathing difficulties, joint, or severe muscle pain; an increase in HR of <20 beats per min; respiratory rate <5 breaths per min over resting respiratory rate.

### Outcome measures

3.3

#### Primary outcome

3.3.1

##### 6-Minute Walking Test

3.3.1.1

The primary outcome is the change in 6-MWD from baseline to the end of the treatment period (week 24). The purpose of this test is to measure the maximum distance that the participants can walk as fast as possible within 6 minutes on a flat surface. The 6-MWT is one of the most widely used tests to assess exercise tolerance in COPD.^[17]^ Participants will be given 400 μg salbutamol aerosol 20 min before the tests for safety.

#### Secondary outcomes

3.3.2

##### Pulmonary function test

3.3.2.1

Pulmonary function is the gold standard parameter for the diagnosis of COPD and is recommended by the GOLD guidelines.^[5]^ The pulmonary function test will be performed by a professional with a designated instrument (JAEGER MasterScreen, CareFusion, Höchberg, Germany). Participants will be administered bronchodilators before the tests. The parameters FEV1, FEV1 predicted, FVC, FVC predicted, and FEV1/FVC will be recorded.

##### St George's Respiratory Questionnaire (SGRQ)

3.3.2.2

The SGRQ includes 3 parts: symptoms, mobility, and social and emotional effects of the disease, which is an important tool for assessing the quality of life of patients with COPD.^[19]^ Study researchers will guide the participants in filling the questionnaire and participants will be required to answer the questions honestly.

##### Modified Medical Research Council Dyspnea Scale

3.3.2.3

The Modified Medical Research Council Dyspnea Scale is classified into 5 grades (0–4) based on the severity of dyspnea and can be completed in 30 seconds. Presently, it is widely used for assessment of dyspnea assessment as well.^[20]^

##### COPD Assessment Test

3.3.2.4

The CAT was presented by Jones based on the SGRQ in 1991. The CAT includes parameters such as symptoms, exercise capacity, psychology, sleep, and impact of society. It is a very important tool for assessing the severity of COPD symptoms.^[19]^

##### Hospital Anxiety and Depression Scale

3.3.2.5

The Hospital Anxiety and Depression Scale is a self-administered questionnaire used to screen for the presence of depression and anxiety and has been shown to be a valid and reliable measure of severity of emotional disorders used in general practice.^[21]^ Participants will be instructed to choose one response from the given answers that best describes their current feelings.

##### Exacerbation frequency

3.3.2.6

The number of acute exacerbation episodes of COPD (at week 36). COPD exacerbation is defined as an acute worsening of respiratory symptoms resulting in the requirement of additional therapy.^[22]^

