### Termination and withdrawal criteria

2.8

All participants will be informed that they have the right to withdraw from the trial at any point and that they will be provided with standardized treatment if they withdraw. The reason for withdrawal will be recorded in their case report file. The criteria for stopping treatment and withdrawing patients from the clinical trial are as follows: the participant developed adverse event due to TNHCG exercise, and the investigator believes it is not appropriate for them to continue the trial; the participant developed severe exacerbation of COPD; the participant developed another severe disease that needs to be treated during the study; poor compliance; the patient participated in another similar trial simultaneously.

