### Statistical analysis

3.8

All analyses will be conducted according to the intention to treat principle. Missing values will be replaced by the last observation carried forward method. Two similar participants with complete data will be double-checked to make sure that data are correct before analysis.

The data will be analyzed using the Statistical Package for the Social Sciences version 23.0 (SPSS 23.0, Chicago, IL). The analytical methods will be selected according to the distribution characteristics of the data: measurement data will be analyzed using group *t* tests or nonparametric tests, while count data will be analyzed using a Chi-square test or the Fisher exact probability method. Grade data will be analyzed using nonparametric tests. Compared with baseline values, measurement data will be assessed using paired *t* tests or nonparametric tests, and count data will be examined using a nonparametric test. All statistical tests will be bilateral tests and *P*-values <.05 will be considered statistically significant.

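### Exacerbation counting stops at a severe exacerbation, and the partial count is carried forward to week 36 with no allowance for time at risk

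*Protocol article*

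**What the plan says.** Section 3.3.2.6 makes the outcome a number per patient: "The number of acute exacerbation episodes of COPD (at week 36". It also says what counts: "COPD exacerbation is defined as an acute worsening of respiratory symptoms resulting in the requirement of additional therapy". A severe exacerbation is therefore one of the events to be counted.

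Section 2.8 introduces its list with "The criteria for stopping treatment and withdrawing patients from the clinical trial are as follows", so stopping the exercise and leaving the trial are one rule. The list includes "the participant developed severe exacerbation of COPD". It also includes "the participant developed adverse event due to TNHCG exercise", which only the exercise arm can meet, and poor compliance.

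Section 3.8 states an intention-to-treat analysis and then, with no endpoint excepted, "Missing values will be replaced by the last observation carried forward method". Its test list reads "measurement data will be analyzed using group" *t* tests or nonparametric tests, and "count data will be analyzed using a Chi-square test or the Fisher exact probability method". Graded data go to nonparametric tests. None of these uses length of follow-up.

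Section 3.5 adds only a general intention to keep following randomised patients.

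**The concern.** Each rule is common in isolation. The problem is their combination for this one outcome. A patient who has a severe exacerbation is withdrawn, so later episodes go unrecorded. LOCF then enters the number so far as if 36 weeks had been observed. The patients cut short are those with the most events, and an arm with more severe events loses more of its episodes.

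Early exit for other reasons shortens the count in the same way. Because one withdrawal reason applies to the exercise arm alone, exit may be unequal between arms.

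At stake is the estimate for a named secondary outcome. A true reduction could be understated, or a spurious one produced, depending on who leaves and why. The article fixes these rules itself, so this is not detail left to an analysis plan.

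**Working it through.** **The plan's own figure.** No figure is given for exacerbations. The sample size in section 2.4 concerns 6-minute walk distance (6MWD). With 52 m, 77.5 used as a standard deviation, two-sided 5% and power 0.90: 2 × (1.960 + 1.282)² × 77.5² / 52² = 46.7, or 47.66 with the t distribution, so 48 per arm; 48 / 0.8 = 60. It reproduces, and is used here only for the 60 per arm.

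**Inputs from the article.** Horizon 24 + 12 = 36 weeks (section 2.1); withdrawal at a severe exacerbation (2.8); LOCF and the test list (3.8). I take the recorded value to be the cumulative count.

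**Assumed inputs, not in the article.** Control mean m = 0.8 or 1.2 episodes over 36 weeks; negative binomial dispersion k = 0.8; proportion severe p = 0.25; true rate ratio 0.50 or 0.60.

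**Step 1: recorded count when counting stops at the first severe episode.** For a patient with expected count μ over 36 weeks, the expected recorded count is (1 − e^(−pμ)) / p. Averaging over gamma variation between patients gives

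E(m) = [1 − (1 + k p m)^(−1/k)] / p.

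Example, m = 0.8: kpm = 0.16; 1.16^(−1.25) = 0.831; E = 0.169 / 0.25 = 0.677. For the TNHCG arm at ratio 0.50, m = 0.4: 1.08^(−1.25) = 0.908; E = 0.092 / 0.25 = 0.367.

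| Control mean | True ratio | Control recorded | TNHCG recorded | Apparent ratio |
|---|---|---|---|---|
| 0.8 | 0.50 | 0.677 of 0.80 | 0.367 of 0.40 | 0.54 |
| 0.8 | 0.60 | 0.677 of 0.80 | 0.433 of 0.48 | 0.64 |
| 1.2 | 0.50 | 0.943 of 1.20 | 0.528 of 0.60 | 0.56 |
| 1.2 | 0.60 | 0.943 of 1.20 | 0.619 of 0.72 | 0.66 |

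Simulation of the same scenarios gave 0.54-0.56 and 0.63-0.66, in agreement.

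**Step 2: other assumptions.** With 0.8 to 1.8 episodes per year (times 36/52), k = 0.7, p = 0.2 to 0.5 and a true ratio of 0.65, the formula gives apparent ratios of 0.67 to 0.74, with the control arm keeping 91% down to 65% of its episodes. Simulation gave 0.65-0.76 and 93% down to 64%; the slightly wider range is Monte Carlo error.

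**Step 3: power and type I error, 60 per arm.** Under the Step 1 assumptions, t-test power falls by about 4 to 12 points when counts are cut short. A check with 2,000 replicates per scenario gave 0.65 to 0.58, 0.42 to 0.36, 0.73 to 0.64 and 0.50 to 0.41, in table order. With no true effect and equal exit, rejection stayed near 5%.

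**Step 4: unequal exit, no true effect.** Assume 10% of control and 30% of TNHCG patients leave at a uniformly distributed time. Mean observed time is then 1 − 0.10/2 = 0.95 and 1 − 0.30/2 = 0.85 of the period, so carried-forward counts give 0.85 / 0.95 = 0.89. With withdrawal at severe episodes added (30% severe), simulation gave 0.90-0.92. Episodes divided by observed time gave 0.99-1.02.

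**Step 5: is an offset enough?** In the Step 2 scenarios, dividing episodes by observed time moved the apparent ratio for a true 0.65 to 0.63-0.71 in simulation. The expected value, using mean observed time as the average of (1 − e^(−pμ)) / (pμ), is 0.66 to 0.68. Most of the bias goes, but not all, because the patients with the highest rates still contribute the least time.

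**The case against.** The strongest reply is that the article does not settle that counting stops. Section 3.5 intends continued follow-up and section 3.8 invokes intention to treat. That is fair as far as it goes, but a general retention aim does not override an explicit list of reasons for withdrawal from the trial. The three sections point different ways, and nothing says which governs this outcome.

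It can also be said that the size is modest and rests wholly on assumed rates, and that choosing a count model is normally left to an analysis plan. Both are true. They limit the grade of the point, but the article does fix the withdrawal rule and LOCF.

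Three stronger readings are tempting and should not be drawn:

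- **That the episode number will be tested by chi-square, losing repeat episodes and much power.** Paired with Fisher's exact test, the article's term for count data most likely means categorical frequencies, so the episode number would go to a t or rank test. On full counts in the four scenarios, t-test power was 0.64, 0.41, 0.74 and 0.51, against 0.66, 0.43, 0.76 and 0.54 for negative binomial regression. With complete follow-up the test list is not the problem.
- **That the bias always runs toward no difference.** Withdrawal at severe episodes does pull that way, but extra early exit in the TNHCG arm favours TNHCG.
- **That false positives are clearly inflated.** With equal exit they are not. With 10% against 30% exit, rejection was about 7% in 500 runs for the t test, but similar for the model with an offset, so those runs do not separate the methods. The distortion shown is in the estimate.

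**Conclusion.** The point holds in this form: followed as written, sections 2.8 and 3.8 truncate the exacerbation count at one of its own events and present the result as a 36-week count. Under the stated assumptions, true ratios of 0.50 and 0.60 appear as about 0.54-0.56 and 0.63-0.66, with 4 to 12 points of t-test power lost. With heavier event rates and a larger severe share the shift grows; with the mildest inputs it is negligible. Unequal exit of 10% against 30% would turn no effect into an apparent ratio of about 0.90-0.92 in favour of TNHCG. The net direction cannot be fixed in advance, and no size can be derived from the article alone, since rates, severe share, dispersion and exit by arm are all assumed.

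This should be corrected, but it concerns one secondary outcome. It says nothing about the primary 6MWD analysis.

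**What to change.** 1. Reconcile sections 2.8, 3.5 and 3.8 so that exacerbations are recorded to week 36 for every randomised patient who still consents, whether or not the exercise was stopped. When the exercise stops is a clinical matter, and no change to it is proposed here; only data collection is separated from it.
2. Exempt this endpoint from LOCF.
3. Analyse the number of episodes from randomisation to week 36 with a count model, for example negative binomial regression, with log follow-up time as offset, and report the rate ratio with its 95% confidence interval.

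Item 3 without item 1 leaves part of the event-driven bias, so both are needed.

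The cost is analysis wording plus continued recording at visits already planned. Section 5.1 reports recruitment as under way, so the change could be made for patients still to be followed.

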### Safety assessment

3.4

TNHCG, which is mainly composed of Wudang tortoise-shaped posture exercises has been used for disease treatment, health care, and rehabilitation for more than 2000 years in China. It includes low to medium intensity exercises and previous studies have confirmed that it has a good effect on COPD rehabilitation with few adverse reactions.^[11–13]^ In this study, all procedures will strictly follow the standard operation procedure (SOP) of TNHCG exercise. Moreover, laboratory tests will be performed to analyze blood; urine; feces; and heart, liver, and kidney function; from the time of enrollment through the treatment period.

### Compliance

3.5

The participants will be informed about test content, course of intervention, and adverse effect of the trial in detail before being allocated to a group. Once patients have been randomized, researchers will make an effort to follow the patient for the duration of the study. At each visit, adherence to interventions will be monitored, the results of all examinations explained, and all trial or transportation costs will be covered. Before every visit, messages will be sent through media such as WeChat, QQ, or by phone to remind patients of the upcoming visit for data collection. Otherwise, free registration and treatment advice will be provided to the participants in the follow-up period.

### Adverse events

3.6

Any adverse events will be recorded in the CRFs irrespective of their relationship to the study intervention. In case of any serious adverse events, the intervention will be immediately stopped and a detailed description of the time, severity, relationship with TNHCG exercise, and the measures taken based on standard procedures of the China Food and Drug Administration will be recorded. In addition, serious adverse events will be reported to the Steering Committee and Ethics Committee within 24 hours.

### Data management and quality control

3.7

All data will be recorded in the CRFs, which will be completed by trained and qualified investigators. Once a CRF is completed, the original record will not be changed if any corrections are made. The completed CRFs will be reviewed by the clinical inspector. Data entry and sorting will be performed using EpiData 3.1 software; 2 data administrators will input and proofread the data independently. After reviewing and confirming that the established database is correct, the data will be locked by the main researchers and statistical analysts. All data management will be according to the standard procedures. The evidence-based Medicine Center at the Sichuan TCM hospital (Chengdu, China), which does not have any competing interests, will be responsible for monitoring the data. The Department of Science Research of the hospital at Chengdu University of TCM, which is independent of the investigators, will perform data audits during the trial.

### Statistical analysis

3.8

All analyses will be conducted according to the intention to treat principle. Missing values will be replaced by the last observation carried forward method. Two similar participants with complete data will be double-checked to make sure that data are correct before analysis.

The data will be analyzed using the Statistical Package for the Social Sciences version 23.0 (SPSS 23.0, Chicago, IL). The analytical methods will be selected according to the distribution characteristics of the data: measurement data will be analyzed using group *t* tests or nonparametric tests, while count data will be analyzed using a Chi-square test or the Fisher exact probability method. Grade data will be analyzed using nonparametric tests. Compared with baseline values, measurement data will be assessed using paired *t* tests or nonparametric tests, and count data will be examined using a nonparametric test. All statistical tests will be bilateral tests and *P*-values <.05 will be considered statistically significant.

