### Sample size

2.4

Sample size calculations are based on the primary outcome (improvement in the 6-MWT). Referring to previous research by Chen et al,^[17]^ compared to the conventional treatment group, the 6-minute walking distance (6MWD) of the COPD TaiChi PR group improved by an average of 52 m (variance 77.5, correlation coefficient 0.7–0.8, power 0.90). Power analysis revealed that 96 participants, 48 in each group are required to attain a significance level of 2.5%. To avoid the decrease in sample size caused by follow-up drop-outs, the total sample size required, calculated with a 20% drop-out rate, is 120 participants with 60 participants per group.

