### Randomization and blinding

2.5

A professional statistician with expertise in evidence-based traditional Chinese medicine in the Sichuan province will generate 120 random serial numbers using SAS 9.2 software (SAS, Cary, NC). Randomization will be performed after screening and baseline assessment, and eligible patients with COPD will be assigned to the trial group or the control group in a 1:1 ratio. The allocation sequence will be kept in sequentially numbered, sealed, and opaque envelopes. The envelopes will be kept safe and opened only by a designated administrator who will not directly participate in the recruitment or follow-up of any participant. The main investigator, data manager, data analyst, and outcome evaluators will be blinded to the group allocations. Participants and TNHCG instructors who supervise the exercise will not be blinded to the allocation. Once the groups are allotted, the TNHCG instructors will receive a copy of the participant number and allocation, and the outcome assessor will be informed of the participant number only.

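### Last observation carried forward, the only stated rule for missing values, biases the week-24 change in 6-minute walk distance

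*Protocol article*

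**What the plan says.** The section Statistical analysis (3.8) of the protocol article commits to intention to treat ("All analyses will be conducted according to the intention to treat principle") and then fixes how gaps are filled: "Missing values will be replaced by the last observation carried forward method". It names no outcome to which this does not apply. The completed data go into group t tests or nonparametric tests, and "All statistical tests will be bilateral tests" at 0.05.

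Section 3.3.1.1 defines the endpoint: "The primary outcome is the change in 6-MWD from baseline to the end of the treatment period (week 24").

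The Sample size section (2.4) takes from an earlier Tai Chi trial that 6MWD "improved by an average of 52 m (variance 77.5, correlation coefficient 0.7–0.8, power 0.90"), concludes that "96 participants, 48 in each group are required to attain a significance level of 2.5" per cent, and allows for losses: the total, "calculated with a 20% drop-out rate, is 120 participants with 60 participants per group".

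The section Termination and withdrawal criteria (2.8) lists among its reasons an adverse event caused by the exercise, a severe exacerbation, another severe disease and poor compliance.

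**The concern.** With 20% drop-out, up to 24 of the 120 primary values (0.20 × 120) would be carried forward. A patient with no walk after baseline is scored as exactly zero change. A patient who leaves later keeps a mid-treatment value as the week-24 result. Neither is a credible estimate of the week-24 change in a disease that can worsen or recover over 24 weeks.

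The withdrawal reasons make this more than a technicality. One of them, an adverse event due to the exercise, can arise only in the exercise arm, so losses may be unequal. Another, severe exacerbation, is related to the outcome, and carrying forward the earlier walk hides the deterioration. What is at stake is the size of the primary effect, the validity of its interval and, if losses are unequal, the false-positive rate.

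**Working it through.** **1. The plan's own figure.** Inputs from section 2.4: difference 52 m, spread 77.5, power 0.90, drop-out 20%. The 77.5 is labelled a variance but reproduces the sample size only as an SD of 77.5 m. Using n = 2 × SD² × (z₀.₉₇₅ + z₀.₉₀)² / Δ²:

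2 × 77.5² × (1.960 + 1.282)² / 52² = 46.7, so 47 per group. The t-test version gives 47.7, so 48. Then 48 / 0.8 = 60 per group, 120 in total. The stated size is reproduced, with 2.5% read as one-sided, which matches the two-sided 5% of section 3.8.

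**2. What the rule estimates.** If a fraction p of an arm is missing at random, the true mean change is m and the mean carried value is c, the expected arm mean is (1 − p) × m + p × c. Figure 2, which holds the visit schedule, is not shown, so two cases are given. The 20% is applied to each arm and control change is set to 0.

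- All drop-outs carry baseline (c = 0): 0.8 × 52 = 41.6 m, a bias of −10.4 m.
- All carry an interim value at half the effect (assumed, c = 26 m): 0.8 × 52 + 0.2 × 26 = 46.8 m, a bias of −5.2 m.

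**3. Standard error and coverage.** In the baseline case the variance of the filled data is 0.8 × 77.5² + 0.8 × 0.2 × 52² in the exercise arm (SD 72.4 m) and 0.8 × 77.5² in the control arm (SD 69.3 m).

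- Reported SE = √((72.4² + 69.3²) / 60) = 12.9 m.
- SE from 48 observed patients per arm = 77.5 × √(2/48) = 15.8 m, so the reported SE is about 18% smaller (1 − 12.9/15.8).

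Simulation of 20,000 trials (60 per arm, two-sided 5% t test, interim-to-final correlation of change 0.75 assumed):

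| Case, 20% drop-out per arm | Estimate (m) | Mean reported SE (m) | SD of the estimate (m) | Coverage of 52 m | Power |
|---|---|---|---|---|---|
| Baseline carried | 41.6 | 12.9 | 12.9 to 13.0 | about 87% | 0.89 |
| Interim carried | about 47 | 14.2 | 14.2 to 14.3 | about 93% | about 0.90 |

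The reported SE agrees with the estimator's own sampling spread. The loss of coverage therefore comes mainly from bias. A t test on 48 observed patients per arm has power 0.90.

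**4. Unequal drop-out.** The splits and the drift are assumptions; the document gives one overall rate.

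With a true 52 m and baseline carried:

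- 30% exercise / 10% control: 0.7 × 52 = 36.4 m, power about 0.80.
- 10% / 30%: 0.9 × 52 = 46.8 m.

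With no treatment effect, both arms drifting by −30 m, and 30% / 10% drop-out:

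- Baseline carried: 0.7 × (−30) − 0.9 × (−30) = −21 + 27 = +6.0 m.
- Half carry baseline and half an interim value (mean carried −7.5 m): −23.25 + 27.75 = +4.5 m.
- All carry an interim value (mean carried −15 m): −25.5 + 28.5 = +3.0 m.

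A drift of +30 m reverses each sign. Simulated type I error:

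| Values carried | Change SD 77.5 m | Change SD 54.8 m |
|---|---|---|
| All baseline | 7.4% to 7.8% | about 10% |
| Half baseline, half interim | 6.2% to 6.7% | about 7.5% |
| All interim | about 5.5% | about 6% |

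The second SD is what follows if 77.5 m is the SD of a single walk and the correlation is 0.75, the middle of the stated 0.7 to 0.8: 77.5 × √(2 × (1 − 0.75)) = 54.8 m.

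**5. Where the rule does no harm to the type I error.** With no treatment effect, equal 20% drop-out and a common 30 m decline, rejection is about 5%. With 30% / 10% drop-out and no drift, it is also about 5%.

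**The case against.** The strongest defence is that on the plan's own assumptions the rule is conservative: the effect shrinks and power hardly moves. The 41.6 m is a boundary case that needs every drop-out to lack a post-baseline walk. False positives need unequal losses and a common drift together, and neither figure is in the document. Section 3.5 also commits the researchers to try to follow patients for the whole study, which should limit missing data. All of this stands, and it limits the severity. It does not rescue the rule. A shrunken estimate with an interval that misses too often is still a wrong answer for the primary outcome, and the direction of the bias cannot be known in advance.

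Three stronger readings are tempting but not supported.

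- A reader might infer that carrying values forward understates the standard error of the estimate. It does not in the cases simulated: reported and actual spread agree. The 12.9 m is small only beside the 15.8 m that the observed week-24 data support, and those are two different estimators.
- A reader might see a contradiction between sizing on 96 patients and analysing 120. Inflating enrolment for drop-out and then analysing everyone randomised is ordinary practice.
- A reader might pair a 4.5 m bias with a type I error near 7.5% at a change SD of 77.5 m. At that SD the 4.5 m case gives about 6.2% to 6.7%; about 7.5% belongs to an SD of 54.8 m.

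The absence of a sensitivity analysis is not itself a fault, since that is commonly left to an analysis plan.

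**Conclusion.** The point holds as a matter of bias. The article states the rule outright, nothing in the visible text softens it, and it governs the primary result.

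The 52 m difference shrinks by about 5 to 10 m at the planned drop-out, and a nominal 95% interval covers the true value about 87% to 93% of the time. This assumes random drop-out of 20% in each arm and a change SD of 77.5 m; the upper end also assumes an interim value at half the effect.

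The false difference of about 4.5 to 6 m and the raised type I error are illustrations under assumed 30% / 10% losses and a 30 m drift, with at least half of the drop-outs carrying baseline. They show that the direction can reverse; they do not predict what this trial will see. The change should be made, but the plan's power and sample size are not undermined by it.

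**What to change.** Replace the carried-forward sentence in section 3.8. Analyse 6MWD with a likelihood-based repeated-measures model over the scheduled post-baseline walks, with baseline 6MWD as covariate. If the schedule has only one post-baseline walk, use multiple imputation by arm instead. Both rest on data being missing at random, which the withdrawal reasons in section 2.8 make doubtful, so add one sensitivity analysis for data missing not at random. Keep carrying forward at most as a further sensitivity analysis.

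No new data are needed. The cost is an amended analysis paragraph, modest programming time and a somewhat wider interval. In the case where drop-outs have only a baseline walk, the SE moves from 12.9 m toward the 15.8 m that the observed patients support, before any gain from adjusting for baseline. Section 5.1 says recruitment was still under way, so the change could be made before the database is locked.

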### Eligibility criteria

2.7

Inclusion criteria:

1.Patients aged 40 to 75 must meet the diagnostic criteria of COPD according to the GOLD guidelines; no gender and grade limitations.2.Patients with acute exacerbation periods must first be relieved before they can participate in the trial, while patients with stable COPD meet the inclusion criteria.3.Patients have no heart, liver, kidney, or mental system issues.4.Patients provide written informed consent.

Exclusion criteria:

1.Participants with other chronic respiratory diseases.2.Participants with severe comorbidities, such as tumors, symptomatic cardiovascular diseases, myocardial infarction, and neuromuscular diseases.3.Participants who are pregnant or lactating.4.Participants with AIDS, mental illnesses, and cognitive dysfunction.5.Participants who are currently practicing traditional Qigong exercises such as Baduanjin and TaiChi or are participating in other clinical trials associated with COPD.

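### The primary 6MWD comparison is an unadjusted t test or rank test chosen from the data; one baseline-adjusted model would fix the estimand and add modest precision

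*Protocol article*

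**What the plan says.** Section 3.3.1.1 of the protocol article defines the endpoint: "The primary outcome is the change in 6-MWD from baseline to the end of the treatment period (week 24". Baseline 6MWD is therefore needed for every participant, and it is available before allocation, since section 2.5 states that "Randomization will be performed after screening and baseline assessment".

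For the comparison between groups, section 3.8 states "The analytical methods will be selected according to the distribution characteristics of the data" and then "measurement data will be analyzed using group *t* tests or nonparametric tests". It names no covariate, does not say which of the two tests is primary for 6MWD, and gives no rule for moving from one to the other. Paired tests against baseline are listed separately, for changes within a group.

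Section 2.4 sizes the trial on a between-group difference in mean walking distance: the reference group "improved by an average of 52 m", with "variance 77.5" and "correlation coefficient 0.7–0.8". No later step uses the correlation. Section 2.7 admits patients with "no gender and grade limitations", so a wide spread of baseline walking distance can be expected.

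**The concern.** Two features of the stated method are weaker than they need to be.

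**The target of the primary analysis is open.** A t test on change goes with a difference in mean change, in metres. A rank test compares distributions and does not estimate that difference. The sample size rests on 52 m, so a switch to a rank test would leave the primary result on a different footing from the one the trial was designed on. As worded, the observed data decide which applies.

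**Baseline is used with the wrong weight.** Subtracting baseline is optimal only if the slope of week-24 on baseline 6MWD equals one. With equal standard deviations (SDs) at the two times that slope is the correlation r, which the protocol puts at 0.7–0.8. With a slope below one, the arm that by chance starts lower tends to gain more. Subtraction therefore over-corrects the imbalance, and the surplus stays in the estimate as noise.

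At stake are a clear statement in advance of what the primary result is, and some precision that could be had from data already collected.

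**Working it through.** **Inputs.** From section 2.4: difference 52 m, 77.5 (printed as a variance), r = 0.7–0.8, power 0.90, 48 per group evaluable, 20% drop-out, 120 in total. From section 3.8: two-sided 5%.

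**Assumptions.** (a) 77.5 is an SD in metres; as a variance it would give an SD of 8.8 m and about one patient per group. (b) r is the correlation between baseline and follow-up 6MWD. (c) The SD of 6MWD is the same at both times. The protocol does not say whether 77.5 is the SD of 6MWD or of its change, so both are shown.

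**Step 1: the protocol's own figure.** n per group = 2 × (1.960 + 1.282)² × 77.5² / 52² = 46.7, so 47. The exact t calculation gives 47.66, so 48. Then 96 / 0.8 = 120. Both stated figures reproduce, as an unadjusted two-sample t test in which 77.5 is the SD of the analysed variable and r plays no part. If 77.5 were the SD of 6MWD and r were used to obtain the SD of change, the formula would give 29 (r = 0.7) or 19 (r = 0.8) per group.

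**Step 2: variance ratio.** With s the SD of 6MWD:
- change-score t test: variance 2(1 − r)s²
- ANCOVA: variance (1 − r²)s²
- ratio: (1 + r)/2 = 0.85 (r = 0.7) or 0.90 (r = 0.8)

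The standard-error ratio is √0.85 = 0.922 or √0.90 = 0.949, a cut of 8% or 5%. In patients, 1/0.85 = 1.18 and 1/0.90 = 1.11. The ratio does not depend on how 77.5 is read.

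**Step 3: 95% CI half-width, 1.96 × SD × √(2/48).**

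| Reading of 77.5 | r | SD, change | SD, ANCOVA | Half-width, change | Half-width, ANCOVA |
|---|---|---|---|---|---|
| SD of 6MWD | 0.7 | 60.0 | 55.3 | 24.0 m | 22.1 m |
| SD of 6MWD | 0.8 | 49.0 | 46.5 | 19.6 m | 18.6 m |
| SD of change | 0.7 | 77.5 | 71.5 | 31.0 m | 28.6 m |
| SD of change | 0.8 | 77.5 | 73.5 | 31.0 m | 29.4 m |

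With all 60 per arm analysed, every half-width shrinks by √(48/60) and the ratios are unchanged.

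**Step 4: power at 48 per group, two-sided 5% (normal approximation).** If 77.5 is the SD of change, power is 90.8% for the t test and 94.6% (r = 0.7) or 93.4% (r = 0.8) for ANCOVA. If it is the SD of 6MWD, power is 98.9% or 99.9% for the t test on change and at least 99.6% for ANCOVA.

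**Step 5: size of the over-correction.** Take 77.5 as the SD of 6MWD and 60 per arm. The baseline difference has standard error 77.5 × √(2/60) = 14.1 m, so its 95% limit is 27.7 m. An imbalance of that size shifts the change-score estimate by (1 − r) × 27.7 = 8.3 m (r = 0.7) or 5.5 m (r = 0.8), in the direction opposite to the imbalance. On average over randomisations the shift is zero, and the t test's standard error already includes it. It is the same loss as in step 2, seen from another side.

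**Step 6: type I error of the open choice.** In a simulation with 48 per group and 10,000 runs, choosing between the t test and the rank test by a Shapiro test gave 0.048 for normal and 0.053 for lognormal data. Reporting the smaller of the two P-values gave 0.057 and 0.069.

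**The case against.** The best defence is that the endpoint is already a change score. A reader might infer from the word unadjusted that the comparison ignores baseline, or that it is biased by imbalance. Neither follows: each participant's baseline is subtracted and the test is unbiased under randomisation. What remains is the efficiency argument about the weight.

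A much larger gain is also tempting to quote. Against a t test on week-24 values alone, ANCOVA would have 1 − r² = 0.36–0.51 of the variance. The protocol does not plan that analysis for its primary outcome, so the figure is not a measure of what is lost here.

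A reader might further infer that choosing the test from the data inflates the false-positive rate. The stated criterion is the distribution, not the P-value, and section 2.5 blinds the data analyst. A choice of that kind stays close to 5% in simulation. The higher rates need the smaller P-value to be picked, which is not the stated rule.

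Finally, a condensed article may leave the exact normality rule and any stratification of the randomisation to a fuller document. That is accepted, and neither is counted here. But section 3.8 does state a method, as a choice between two tests that answer different questions, and naming one model would replace that statement rather than fill a gap.

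**Conclusion.** The point holds, at modest size. The planned t test on change is valid, and the trial is not underpowered on its own inputs (90.8% or more at 48 per group, without adjustment). The more important defect is that the wording leaves the primary result as either a mean difference in metres or a rank comparison, although the sample size rests on the former. The second is a loss of precision: ANCOVA would cut the standard error by 5%–8%, narrowing the half-width by 1.0–1.9 m if 77.5 is the SD of 6MWD and by 1.6–2.4 m if it is the SD of change. These figures rest on r = 0.7–0.8 being the baseline to follow-up correlation, on equal SDs at both times and, for the metres, on 77.5 being an SD. It is an improvement worth making, not an error that would invalidate the trial.

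**What to change.** In section 3.8, name one primary analysis: a linear model of week-24 6MWD (or, equivalently for the group effect, its change) on treatment group and baseline 6MWD. Report the adjusted mean difference in metres with its 95% confidence interval. If residuals are clearly non-normal, keep the same estimate and use robust or bootstrap standard errors. Keep a rank-based test as a sensitivity analysis only.

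The continuous secondary outcomes (FEV1, FVC, SGRQ, CAT and HADS scores) can be adjusted for their own baselines in the same way; this is optional.

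The cost is a wording change. It needs no new data, visits or patients. It should be made and dated before any outcome data are unblinded; section 5.1 describes recruitment as still under way.
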